**Methods/design:**

In this randomized controlled trial, 120 patients will be randomly allocated in a 1:1 ratio to *Baduanjin* exercise combined with conventional exercise of CR (*Baduanjin* exercise group) or conventional exercise of CR alone (conventional exercise group). In addition to conventional physical activity, participants in the *Baduanjin* exercise group will participate in a 45-min *Baduanjin* exercise training session twice a week, for 12 weeks. The primary outcome is walking distance in the 6-min Walk Test (6MWT), and the secondary outcomes are peak oxygen uptake (VO_2_ peak), ventilatory anerobic threshold (VAT), The minute ventilation to carbon dioxide production relationship (VE/VCO_2_ slope), left ventricular end-diastolic volume index (LVEDVi), left ventricular ejection fraction (LVEF), quality of life assessed by the Minnesota Living with Heart Failure Questionnaire (MLHFQ), amino-terminal pro-brain natriuretic peptide (NT-proBNP), hs-CRP, heart rate variability (HRV), New York Heart Association (NYHA) classification, and major adverse cardiovascular events.

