**Discussion:**

This is the first trial to evaluate the effects of a *Baduanjin* exercise-based CR program on cardiopulmonary function and exercise tolerance in ischemic CHF patients. If successful, it will prove the value of *Baduanjin* exercise in improving cardiopulmonary function and exercise tolerance in patients with ischemic heart failure on phase-II CR, and may further develop a Chinese *Qigong* exercise-based CR framework.

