Empirical observations have suggested that *Baduanjin* exercise may improve cardiopulmonary function and exercise tolerance [10–12]. A meta-analysis showed that *Baduanjin* exercise can improve left ventricular ejection fraction (LVEF), cardiac output, stroke output and reduce resting myocardial oxygen consumption in elderly patients. Besides, it can also improve the elasticity of vascular, and regulate blood pressure, glucose, and lipid [13–16]. Compared with conventional exercise, *Baduanjin* exercise can additionally relax and ease the mind and spirit, thus improve sleep quality and unhealthy emotions [17]. These features make *Baduanjin* exercise an optimal exercise for patients with CHF, whose daily activity is greatly limited and who suffered a lot physically and mentally after a long period of medical or surgical treatment. Therefore, *Baduanjin* may be a promising exercise for cardiac rehabilitation for CHF.

However, there is a lack of high-quality evidence for the effectiveness of a *Baduanjin* exercise-based cardiac rehabilitation program for patients with ischemic CHF. Therefore, we conduct this randomized controlled trial (RCT) to evaluate the benefits of a *Baduanjin* exercise-based cardiac rehabilitation program in patients with ischemic CHF. We hypothesized that after the 12-week *Baduanjin* practice, patients would have a greater improvement in cardiopulmonary function, exercise tolerance and health-related quality-of-life scores than those practicing conventional exercise alone.

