## Methods/design

### Trial oversight

*Baduanjin* exercise for patients with ischemic heart failure in phase-II cardiac rehabilitation (BEAR) trial is a single-center, parallel-design, prospective RCT, and will be conducted at Fuwai Hospital, Chinese Academy of Medical Sciences, China. One hundred and twenty participants are to be recruited and the recruitment is scheduled to begin in May 2017. Participants will be randomly assigned in a 1: 1 ratio to *Baduanjin* exercise combined with conventional exercise (experiment group) or conventional exercise alone (control group) training for 12 weeks. Outcomes will be measured at baseline, 3 months and 6 months by researchers blinded to group allocation. Change in walking distance in the 6-min Walk Test (6MWT) [18, 19] from baseline to 6 months will be served as the primary outcome parameter, whereas the change in exercise capacity index, such as peak oxygen uptake (VO_2_ peak), ventilatory anerobic threshold (VAT), the minute ventilation to carbon dioxide production relationship (VE/VCO_2_ slope) determined by cardiopulmonary exercise test (CPET) [20, 21], LV end-diastolic volume index (LVEDVi), and left ventricular ejection fraction (LVEF) assessed using echocardiography, scores assessed using life quality of the Minnesota Living with Heart Failure Questionnaire (MLHFQ) [22], amino-terminal pro-brain natriuretic peptide (NT-proBNP), high-sensitivity C-reactive protein (hs-CRP), heart rate variability (HRV), major adverse cardiovascular events (MACE), and NYHA classification, will serve as secondary outcome parameters. The study protocol and consent documents have been reviewed and approved by the Ethics Committee of Xiyuan Hospital of China Academy of Chinese Medical Sciences (reference number: 2013XL063–1). If there is any amendment to the protocol, approval must be again sought from the Ethics Committee. The study has been registered at ClinicalTrials.gov (NCT03229681), and the trial will be performed in accordance with the principles of the Declaration of Helsinki and Good Clinical Practice guidelines.

Study flow of the trial is illustrated in Fig. 1 and described in detail below according to the Consolidated Standards of Reporting Trials (CONSORT) 2010 Statement [23] and the Standard Protocol Items: Recommendations for Interventional Trials (SPIRIT) Checklist (see Additional file 1).

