### Statistical analysis

Continuous variables will be presented as the mean ± standard deviation (SD), median or interquartile range (IQR), and categorical variables as frequencies or percentages. Comparability of the baseline data between the two groups will be assessed using a two-sample Student’s *t* test for continuous variables, and the chi-square test or Wilcoxon test for categorical variables. Questionnaire score data, known as non-normally distributed data, will be transformed or analyzed with a nonparametric test.

Analysis of the primary outcome will be conducted according to the intention-to-treat (ITT) principle. The ITT set includes all patients randomized, and the per-protocol set consists of all patients with no major deviation from the protocol and with an adherence rate of 80% or higher at the end of the study. The safety set consists of ITT patients excluding those who receive no CR program or who have no safety record after randomization. We will assess the effect of any missing data on the final results by sensitivity analysis. Dropouts will be included in the analysis by modern imputation methods for missing data.

For all analyses, all tests will be two tailed and a statistical probability of < 0.05 is considered statistically significant. All analyses will be conducted using SPSS 18.0 software (SPSS, Inc., Chicago, IL, USA), unless otherwise noted.

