## Discussion

We conducted this trial by trying to assess whether the addition of *Baduanjin* to conventional CR exercise will further improve exercise endurance, reserve of heart function and quality of life, and, if successful, this trial should provide a promising exercise program for CR. As a matter of fact, the building and development of CR is still under exploration, and currently, CR, mainly consists of contemporarily popular exercise. As a traditional Chinese *Qigong*, *Baduanjin* has long been practiced for health care since it has the function of regulating organs and dredging the channels and collaterals [10, 11]. This exercise is especially suitable for patient with CHF complicated with CAD whose activity tolerance is poor because the action of *Baduanjin* exercise is simple and gentle. However, its effect has not been confirmed by objective evaluation.

There are several strengths of our trial. First of all, we use the objective and quantitative Cardiopulmonary exercise testing (CPET) to assess the improvement of cardio-pulmonary function, which is reliable and convincing. Second, *Baduanjin* exercise is easy to master and gentle to practice for CHF patients, which encourages compliance. Moreover, if proved to be effective, the costless *Baduanjin* could be a widely welcomed exercise for CR. On the one hand, it saves time and facilitates for CHF patients who have poor activity tolerance. On the other hand, it may have the effect of improving the prognosis for patients with ischemic CHF, finally it may reduce the social medical expenditure.

A potential limitation of the BEAR trial is that participants and exercise coaches cannot be blinded because it is difficult to conduct blinding in non-pharmacological trials [33]. It is inevitable that performance bias always exists in a practical trial. However, the exercise coaches will not participate in the procedure of recruitment, assessment and data analysis of this study which will minimize bias.

In summary, the BEAR trial will be the first RCT to evaluate the impact of *Baduanjin* exercise on activity tolerance in patients with ischemic CHF and the results of this trial will help to establish the optimal approach for treating patients with CHF and provide reliable evidence for the application of *Baduanjin* exercise in cardiac rehabilitation.

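### The protocol promises proof of better cardiopulmonary function, but only unranked secondary outcomes measure it, each judged at two-tailed p < 0.05 with none named as decisive

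*Protocol article*

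**What the plan says.** The abstract's Methods/design names a single primary and then the secondaries: "The primary outcome is walking distance in the 6-min Walk Test (6MWT), and the secondary outcomes are peak oxygen uptake", followed by ten more outcomes: ventilatory anaerobic threshold (VAT), VE/VCO2 slope, LVEDVi, LVEF, MLHFQ, NT-proBNP, hs-CRP, HRV, NYHA class and MACE. Trial oversight gives the same set and says only that they "will serve as secondary outcome parameters". Neither place ranks them, makes them conditional on the primary, or calls them supportive or exploratory.

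Statistical analysis fixes the decision rule for everything: "For all analyses, all tests will be two tailed and a statistical probability of < 0.05 is considered statistically significant".

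Three passages state what the trial is meant to show:
- Abstract, Discussion: "If successful, it will prove the value of *Baduanjin* exercise in improving cardiopulmonary function and exercise tolerance in patients with ischemic heart failure".
- Background, the hypothesis: "patients would have a greater improvement in cardiopulmonary function, exercise tolerance and health-related quality-of-life scores than those practicing conventional exercise alone".
- Main Discussion, on how the first domain is assessed: "we use the objective and quantitative Cardiopulmonary exercise testing (CPET) to assess the improvement of cardio-pulmonary function, which is reliable and convincing".

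**The concern.** The proof sentence covers two domains, and the design gives a designated test to only one. Walk distance carries exercise tolerance. Cardiopulmonary function is tied to cardiopulmonary exercise testing (CPET), which supplies secondary outcomes only, and no CPET variable is singled out.

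Unadjusted secondaries beside one primary are ordinary practice when they are read as supporting evidence. Here a rule that calls every p < 0.05 significant is combined with a claim of proof in a domain that has several candidate tests and no chosen one. An author who follows the text could rest that claim on whichever variable reached p < 0.05. The false-positive rate of the claim would then exceed that of a single test.

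**Working it through.** **Step 1. Which outcomes can carry each claim**

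| Domain | Abstract Discussion (proof) | Background (hypothesis) | Outcome that addresses it | Status |
|---|---|---|---|---|
| Exercise tolerance | yes | yes | 6MWT distance | primary |
| Cardiopulmonary function | yes | yes | VO2 peak, VAT, VE/VCO2 slope; possibly LVEF, LVEDVi | secondary |
| Quality of life | no | yes | MLHFQ | secondary |

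The narrow set is m = 3 (CPET only), following the main Discussion. The wider set is m = 5 (adding the two echocardiographic measures). Study outcome measures also lists PVO2 beside VO2 peak. It may be the same quantity named twice, so it is counted once.

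**Step 2. Inputs**
- Level per test: 0.05 two-tailed (Statistical analysis). A false positive favouring Baduanjin therefore has probability 0.025 per test.
- Correlation between the test statistics: not given. Assumed common value ρ, shown at 0, 0.5 and 0.8.
- The protocol states no familywise rate for the secondaries, so there is no figure of its own to reproduce.

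**Step 3. Formulas**

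At ρ = 0, P(at least one p < 0.05) = 1 − 0.95^m, and in the favourable direction 1 − 0.975^m.
- m = 3: 1 − 0.95³ = 1 − 0.8574 = 0.143; 1 − 0.975³ = 1 − 0.9269 = 0.073.
- m = 5: 1 − 0.95⁵ = 1 − 0.7738 = 0.226; 1 − 0.975⁵ = 1 − 0.8811 = 0.119.

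For ρ > 0 the statistics are taken as standard normal with a shared factor u. With c = 1.96, φ the standard normal density and Φ its distribution function:
- Two-sided: 1 − ∫ φ(u) [Φ((c − √ρ u)/√(1−ρ)) − Φ((−c − √ρ u)/√(1−ρ))]^m du.
- Favourable direction: 1 − ∫ φ(u) [Φ((c − √ρ u)/√(1−ρ))]^m du.

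**Step 4. Results, all nulls true**

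| Set | Direction | ρ = 0 | ρ = 0.5 | ρ = 0.8 | One test alone |
|---|---|---|---|---|---|
| 3 CPET | two-sided | 14.3% | 12.5% | 9.8% | 5% |
| 3 CPET | favours Baduanjin | 7.3% | 6.3% | 4.9% | 2.5% |
| 5 (CPET + echo) | two-sided | 22.6% | 18.3% | 12.7% | 5% |
| 5 (CPET + echo) | favours Baduanjin | 11.9% | 9.1% | 6.4% | 2.5% |

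In the narrow set, even at ρ = 0.8, the rate is about twice that of one test (9.8/5 and 4.9/2.5, each 1.96).

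**The case against.** **The full analysis plan may deal with it.** It is not shown, and ranking of secondaries is often left to it. Silence on ranking alone would be no finding. What stands in the article, however, is an affirmative rule for all analyses beside an affirmative claim of proof, and the two do not fit as written.

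**Success most naturally means success on 6MWT.** This is a fair reading: it is the only primary, and the sample size rests on it alone. A reader might infer that the protocol lets one significant secondary prove the case even when 6MWT fails. No passage says that. The primary reading does not rescue the sentence, though. A significant walk-distance result would not by itself show better cardiopulmonary function, so that half of the claim still needs a secondary, and none is named.

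**Eleven secondaries at 0.05.** A reader might compute a false-positive rate over all eleven (43% if independent) and attach it to the trial's claims. The documents do not support this. hs-CRP, HRV, NYHA class and MACE are tied to none of the named claims, and treating MACE and NYHA class as continuous normal statistics is itself doubtful.

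**Quality of life.** A reader might also take it as part of what is to be proved. It appears in the hypothesis and the aims, not in the proof sentence.

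**The echocardiographic measures.** No passage labels LVEF or LVEDVi as cardiopulmonary function. For that reason the three-variable figures come first and the five-variable figures are only a wider case.

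**CPET as reliable and convincing.** That remark concerns measurement quality, not inference. It is used here only to show which outcomes stand for the domain.

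**Conclusion.** The point holds in a limited form. The protocol attaches a proof claim to cardiopulmonary function, measures that domain only through secondaries, calls any of them significant at two-tailed 0.05, and names none as decisive. If any one may be used, the chance of a false-positive result is about 10% to 14% for the three CPET variables (5% to 7% favouring Baduanjin, against 2.5%), and 13% to 23% (6% to 12%) if LVEF and LVEDVi also count.

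These figures assume that no outcome truly differs, that the test statistics are approximately normal, and that they share a common correlation between 0 and 0.8. The correlation is not from the documents.

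The type I error of the 6MWT test is not inflated, and this point does not touch the sample size. The defect lies in what the trial may say it has shown, so it should be corrected but does not threaten the primary analysis.

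**What to change.** Before database lock:
1. In Statistical analysis, confine the confirmatory p < 0.05 rule to the 6MWT contrast. Label all secondaries supportive and report them as estimates with 95% confidence intervals.
2. In the abstract's Discussion, restrict the proof claim to exercise tolerance.

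If the sponsor wants confirmatory claims in the other two domains of the hypothesis, prespecify a fixed sequence that opens only after a significant 6MWT result. One example is VO2 peak at week 12, then MLHFQ at week 12, each at two-sided 0.05, stopping at the first non-significant result. The choice and order are the sponsor's, since the protocol ranks none. The proof sentence would then cover cardiopulmonary function only if that step passes.

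The cost is wording: no added patients, visits or measurements, because the study procedures table already schedules CPET and MLHFQ at month 3. The downside is that a nominally significant secondary outside the sequence can no longer be claimed as proof.

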### Adherence

During the 12-week treatment period, participants will be asked to practice strictly according to the CR training prescription, and will not be allowed to take part in any new, additional exercise programs. All patients will be asked to sign a written commitment to guarantee the adherence at baseline evaluation. During the whole study period, subjects will be supervised to record the daily rehabilitation exercise time. Every week, participates will be called to the Cardiac Rehabilitation Center to practice the conventional or *Baduanjin* exercise guided by trained persons. Throughout the 12-week intervention period, the researchers will give patients attendance cards after each session to record the total sessions the patients have taken part in, and patients who missed a class will be asked to attend a “makeup” class. The percentage of compliance will be documented in the CRF. The rate of patient compliance = (total planned number of times − number of absence) / total number of times × 100%. A compliance rate of greater than 80% is considered as good. Otherwise, less than 80% is considered as poor. Patients will be asked to visit the CR Center regularly according to the study protocol, and researchers will inform them of the visit in advance. Attendance of less than 20% is considered as dropout.

### Sample size calculation

Sample size is calculated, based on the 6MWT, according to the following superiority test formula:$$ {n}_c=\frac{\left(1+\frac{1}{k}\right){\left({\mu}_{1-\alpha }+{\mu}_{1-\beta}\right)}^2{\sigma}^2}{{\left[\left({x}_t-{x}_c\right)-\varDelta \right]}^2}, $$

*n*_*t*_ = *kn*_*c*_, The patients’ numbers were arranged in equal proportion (*k* = 1), a superiority one-sided test was employed. According to result of a previous study [32], *x*_t_ = 512.5, *x*_c_ = 436.2, *δ*_t_ = 50.2, *δ*_c_ = 49.8, *δ* is the estimated standard difference calculated as 50.0, and *Δ* = 0.9, *δ* = 45.0. Setting a type I error rate of alpha at 0.05, *μ*_1-a_= 1.64, and setting a type II error rate of beta at 0.1 (a power of 90%), *μ*_1-β_ = 1.282, the calculated sample size of each group is around 49. Assuming conservatively that 20% may be lost to follow-up within 6 months, the total sample size needed to detect this difference at a 5% level of significance with a power of 90% is 118 patients. For our study, we decided to recruit 120 patients for the convenience of randomization.

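### The sample size rests on a one-sided test against an apparent 45 m margin, but the planned analysis is two-tailed with no margin, so the stated 90% power does not describe it

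*Protocol article*

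**What the plan says.** In the Protocol article, the section on sample size calculation states that "a superiority one-sided test was employed". It continues with "Setting a type I error rate of alpha at 0.05", pairs this with the quantile 1.64, and takes 1.282 for 90% power. Its formula subtracts a quantity Δ from the assumed difference between group means. The means are 512.5 and 436.2, a difference of 76.3, and the SD "is the estimated standard difference calculated as 50.0". The margin is printed as "Δ* = 0.9, *δ* = 45.0". The section reports about 49 per group, 118 in total after a 20% loss allowance, and 120 to be recruited.

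The section on statistical analysis says that "all tests will be two tailed and a statistical probability of < 0.05 is considered statistically significant". It applies this to all analyses, makes no exception for the primary outcome and mentions no margin. The hypothesis at the end of the Background is that the Baduanjin group will improve more than the control group, with no minimum excess.

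**The concern.** The two sections describe different tests. The sample size formula corresponds to a null that the difference is at most Δ, tested one-sided at 0.05. The analysis section, read with the Background, corresponds to a null of no difference, tested two-sided at 0.05. Both the null and the alpha differ, so a power figure calculated for the first cannot be carried over to the second.

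This affects interpretation. A significant two-tailed result would show that the difference is not zero. It would not show superiority by more than 45 m, which is the claim implied by the sample size formula. A reader who takes the 90% at face value will also misjudge which differences the trial can detect.

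**Working it through.** **Inputs.** All come from the sample size section except the level and sidedness of the analysis, which come from the statistical analysis section. No unit is printed for the walking distances; metres are assumed.
- Difference: 512.5 − 436.2 = 76.3.
- SD: 50.0.
- Quantiles: 1.64 (one-sided 0.05), 1.96 (two-sided 0.05), 1.282 (90% power).
- Evaluable per arm: 60 × 0.8 = 48.

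**Reading the margin.** The printed expression has a comma where a multiplication would be expected. The SD symbol has just been set to 50.0, so 0.9 × 50 = 45.0 is the coherent reading. The alternative, a margin of 0.9 m, gives n = 2 × (1.64 + 1.282)² × 50² / (76.3 − 0.9)² = 7.5, so 8 per group, far from 49.

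**Reproducing the plan's figure.** With the 45 m margin, n = 2 × (1.64 + 1.282)² × 50² / (76.3 − 45)² = 42,690 / 979.7 = 43.6, so 44 per group (45 with the t distribution). The stated 49 is not reproduced, and no standard variant tried gives it. The total of 118 follows from 49 × 2 × 1.2 = 117.6; dividing by 0.8 would give 122.5.

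**Per-group size under the two-tailed rule.**
- Margin kept: n = 2 × (1.96 + 1.282)² × 50² / 31.3² = 53.6, so 54 (55 with t).
- No margin: n = 2 × (1.96 + 1.282)² × 50² / 76.3² = 9.03, so 10 (11 with t).

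**Power with 48 evaluable per arm.** SE = 50 × √(2/48) = 10.21 m. Power is approximately Φ(net difference / SE − critical value).

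| Test | Calculation | Power at 76.3 m |
|---|---|---|
| One-sided 0.05, margin 45 m | Φ(31.3/10.21 − 1.645) | 92.2% (91.9% with t) |
| Two-sided 0.05, margin 45 m | Φ(31.3/10.21 − 1.96) | 86.6% (85.9% with t) |
| Two-sided 0.05, null of 0 | Φ(76.3/10.21 − 1.96) | over 99.9% |

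For the two-sided test of zero difference, 90% power is reached at (1.96 + 1.282) × 10.21 = 33.1 m.

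**Sensitivity to loss.** With 10% loss there are 54 per arm and SE = 50 × √(2/54) = 9.62 m. The two-sided margin test then has power Φ(31.3/9.62 − 1.96) = Φ(1.29), about 90%.

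**How far apart the two tests are at 48 per arm.** The two-sided test of zero is significant for an observed difference above about 1.96 × 10.21 = 20 m. The one-sided test against 45 m needs about 45 + 1.645 × 10.21 = 62 m.

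**The case against.** The strongest reply is that the document, read as a whole, already points to one analysis. The Background hypothesis is plain superiority, and the two-tailed rule covers all analyses. The margin could then be only a planning device that made the sample size more cautious. On that reading the trial has ample power on its own assumptions and nothing in the analysis need change. This stands in large part, and it limits the finding. It does not rescue the sample size section, which still attaches its 90% to a test with a different null and a different alpha.

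A reader might infer that the trial is underpowered. The documents do not support that. Two of the three tests in the table exceed 90%. The one that falls short combines the margin from one section with the sidedness from the other, and no section states that test in full. Its shortfall also depends on the loss rate. The 20% is assumed over 6 months, while Table 2 schedules the last walk test at month 3; the trial oversight section names 6 months for the primary outcome, so the applicable loss is uncertain.

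A reader might also infer that an observed difference of, say, 35 m would formally count as both a success and a failure. That requires the 45 m margin to be a decision rule. No section says so; the margin appears only in the formula, and in ambiguous print. An analysis plan that is not shown could contain such a rule, but the published two-tailed rule does not.

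Nor does the 90% belong exactly to the one-sided margin test. With 49 per group that test has 92.7% power, and its own inputs give 44 per group.

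**Conclusion.** Wrong as written. The conflict between one-sided and two-tailed testing is explicit, and nothing in the document resolves it. The margin part rests on reading the printed expression as 0.9 × 50 = 45 m, which is the only reading that comes near the stated size, although it gives 44 per group and not 49.

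The stated 90% power does not describe the planned analysis. With 48 evaluable per arm, the analysis as written has 90% power for about 33 m and over 99.9% for 76.3 m. A two-sided test against the margin would have about 86%, or about 90% if loss were 10%.

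These figures assume that the SD of 50 m applies to the change in walking distance, which is the stated outcome; the document does not say whether it does. The fault lies in the justification and in what a significant result would mean. A lack of power is not shown.

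**What to change.** State one primary null, one sidedness and one alpha, in the same words, in both sections.

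The reading consistent with the Background and the statistical analysis section is a null difference of 0, tested two-sided at 0.05. In that case:
- Remove the margin and the 1.64 from the sample size section.
- Replace the calculation with a justification of the fixed 120 patients: with 96 evaluable after 20% loss, about 90% power for a between-group difference of about 33 m, assuming an SD of 50 m for the change in walking distance.

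If the 45 m margin is a real success criterion, write it into the statistical analysis section as a lower confidence limit above 45 m, and restate the power at the alpha actually used.

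Make the choice before the allocation is unblinded. By October 2017, 68 participants had been included and 43 had completed the intervention, and dropping a margin that was truly intended would relax the success rule mid-trial. The trial oversight section requires renewed Ethics Committee approval for any amendment.

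The cost is that amendment, the rewriting of the affected paragraphs and the loss of the headline power statement. The number of patients does not change.

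### The sample-size figures do not reproduce: the printed formula gives 44 per group, not 49, and the total of 118 multiplies by 1.2 where a 20% loss requires division by 0.8

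*Protocol article*

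**What the plan says.** The Sample size calculation section sizes the trial on the 6-minute walk distance with a formula for superiority by a margin, and says that "a superiority one-sided test was employed". It prints every input: equal allocation, expected means of 512.5 and 436.2, group SDs of 50.2 and 49.8 combined to 50.0, a margin of 45.0, a type I error of 0.05 with z = 1.64, and 90% power with z = 1.282.

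From these it reports that "the calculated sample size of each group is around 49". It then allows for a 20% loss over 6 months and concludes that "the total sample size needed to detect this difference at a 5% level of significance with a power of 90% is 118 patients". Recruitment is rounded up to 120.

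**The concern.** Because the formula and all inputs are printed, the two results can be checked directly. The per-group figure looked too high for the inputs. The total looked as if the loss allowance had been added as a percentage of the required number, when that number should be divided by the proportion retained.

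This section is the only support for the trial's size and power. If its outputs do not follow from its inputs, a reader cannot tell which assumption was really used. The statement that 118 protects the required number against a 20% loss would also be untrue as written. The section is the base for any later power statement too, so an error here carries forward.

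**Working it through.** **Inputs (all from Sample size calculation)**

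- Allocation: k = 1
- Difference in means: 512.5 − 436.2 = 76.3
- SD: √[(50.2² + 49.8²)/2] = 50.0, which reproduces the stated value
- Margin: 45.0. The line is garbled in print (a 0.9 and a 45.0 with separate symbols). It is read here as 0.9 × 50.0 = 45.0.
- z-values: 1.64 (one-sided 0.05) and 1.282 (90% power)
- Loss: 20%

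**Step 1: size per group from the printed formula**

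n = (1 + 1/k)(1.64 + 1.282)² × 50² / (76.3 − 45)²

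= 2 × 8.538 × 2500 / 31.3²

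= 42,690 / 979.69 = 43.58, so **44 per group**, against the stated 49.

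**Step 2: could another reading give 49?**

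| Variant | n per group |
|---|---|
| z = 1.645 in place of 1.64 | 44 |
| SD 50.2 | 44 |
| Exact one-sided t | 45 |
| Two-sided 0.05 | 54 |
| Two-sided 0.05, exact t | 55 |
| Margin 0 or 0.9 | 8 |
| **Stated in the article** | **49** |

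With the other inputs held fixed, 49 would need one of the following: an SD of about 53 (50 × √(49/43.58) = 53.0), a margin of about 46.8 (net difference 29.5), or power of about 93%. The article states none of these.

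**Step 3: the loss allowance**

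- The stated total reproduces by multiplication: 49 × 2 × 1.2 = 117.6, so 118.
- To keep 98 after losing 20%: 98 / 0.8 = 122.5. Per group this is 49 / 0.8 = 61.25, so 62 per group and **124 in total**.
- Check on 118: 118 × 0.8 = 94.4, about **47 per group**, below 49.
- Check on 120: 120 × 0.8 = 96, or **48 per group**, still one below 49.
- Loss that 118 can absorb while keeping 98: 1 − 98/118 = 16.9%, not 20%.

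**Step 4: what the printed inputs require**

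44 / 0.8 = 55 per group, **110 in total**. Starting from the exact-t 45: 45 / 0.8 = 56.25, so 57 per group, 114 in total. Both are below 120.

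**Step 5: power at the planned size, for the one-sided margin test**

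With 48 per group: 31.3 / (50 × √(2/48)) = 3.07; 3.07 − 1.645 = 1.42, giving **about 92%**. With 47 per group, the result of randomising 118, power is also about 92%.

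**The case against.** The best defence is that nothing of substance changes. One slip raises the number and the other lowers it. On the section's own one-sided terms 110 patients would do, so 118 is more than enough and 120 more still, with power of about 92% after a 20% loss. The shortfall against 49 is one patient per group at the planned recruitment, and the text says only that the figure is approximate. All of this stands, and the point should not be read as a claim that the trial is underpowered on those terms. It does not make the two figures correct: a gap of 5 on 44 (11%) is not rounding, and two errors that happen to offset do not validate the derivation.

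Two further arguments have some weight. First, the 20% is loss over 6 months, whereas Study outcome measures and Table 2 place the walk test at month 3, so loss at that point may be smaller. Trial oversight, however, gives 6 months for the primary outcome, and the section itself applies 20% to reach 118. Second, the Statistical analysis section keeps dropouts in the analysis by imputation. Imputation does not restore the information lost with them, so it does not replace a correct allowance.

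Finally, 49 may rest on an input that was not printed. That is possible, and the fix allows for it. The loss step is wrong whatever the origin of 49.

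**Conclusion.** Both stated results are wrong as written. The printed inputs give 44 per group (45 by exact t), not 49. A 20% loss turns 44 into 110 in total, or 49 into 124, but in neither case into 118. The claim that 118 secures 49 per group after a 20% loss fails by about two patients per group.

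The consequence is limited: 120 recruited patients are enough for the one-sided margin test on which the section is built, with about 92% power at 48 per group.

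This rests on reading the margin as 0.9 × 50.0 = 45.0, the only reading that comes near the stated figure, and on taking the 20% as loss for the primary outcome, as the section does. The 92% applies only to the one-sided test. The Statistical analysis section makes all tests two-tailed at 0.05, a separate mismatch. With the same margin that would need 54 per group, and 48 per group would give about 87% power.

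**What to change.** Establish where 49 came from, then correct the section in one of two ways.

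- **If the printed inputs are the intended ones:** state 44 per group, 44/0.8 = 55 per group, 110 in total. Then say that 120 will be recruited, leaving 96 evaluable (48 per group) after a 20% loss, and give the power at that number for the test finally adopted.
- **If 49 came from another input:** state that input, correct the loss step to 62 per group (124 in total), and acknowledge that 120 with a 20% loss leaves 48 per group, with the power recomputed accordingly.

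In either case print the margin line unambiguously as 0.9 × 50.0 = 45.0, if that is what was meant.

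The cost is rewording only. Recruitment stays at 120 and no trial procedure changes.
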